## Abstract

**Background:**

Entertainment-education (E-E) media can improve behavioral intent toward health-related practices. In the era of COVID-19, millions of people can be reached by E-E media without requiring any physical contact. We have designed a short, wordless, animated video about preventive COVID-19 behaviors that can be rapidly distributed through social media channels to a global audience. The E-E video’s effectiveness, however, remains unclear.

**Methods/design:**

This is a multi-site, parallel group, randomized controlled trial comparing the effectiveness of an E-E video on COVID-19 against (i) an attention placebo control (APC) video and (ii) no video. For our primary outcomes, we will measure knowledge about preventive COVID-19 behaviors. We will also use a list randomization approach to measure behavioral intent toward preventative COVID-19 behaviors. In each trial arm, participants will be randomized to a control list or a control list plus an item about social distancing, washing hands, cleaning household surfaces, sharing of eating utensils, and the stockpiling of essential goods. Using an online platform, we will recruit 17,010 participants (aged 18–59 years) from the USA, the UK, Germany, Spain, France, and Mexico.

**Trial registration:**

German Clinical Trials Register #DRKS00021582. Registered on May 12, 2020.

**Discussion:**

This trial will utilize several randomization procedures, list experimentation methods, and state-of-the-art online technology to demonstrate the effectiveness of an E-E video to improve knowledge of, and behavioral intent toward, the prevention of COVID-19. Our results will inform future E-E video campaigns for COVID-19 and similar public health intervention needs.

## Background and rationale

A large amount of information about novel coronavirus (COVID-19) has been disseminated by the traditional mass media since the outbreak of the pandemic [1–3]. However, it is not clear if this dissemination has improved knowledge of, or intent toward, preventive COVID-19 behaviors. By preventive behaviors, we mean the public’s adoption of practices, such as social distancing, reduced physical contact, and hand/surface sanitization (among others), to reduce the spread of COVID-19.

Arguably, one possible limitation of mainstream mass media is that it has been perceived as politicized and culturally localized, thus limiting the persuasiveness of messages about COVID-19 prevention [4, 5]. It is also likely that traditional mass media channels (e.g., local or national television networks) have missed key segments of the population, such as young people (25–40 years) who are disproportionately more likely to transmit the virus to older people (≥ 50 years) [6]. An effective public health response could therefore benefit from entertainment-education (E-E) approaches that increase COVID-19 prevention outcomes [7].

To improve knowledge and behavioral intent toward COVID-19 prevention, we have designed an animated, wordless, E-E video that can be rapidly distributed to a diverse and global audience through social media channels. With a short duration (approximately 2.30 min), the E-E video contains no speech and minimizes cultural signifiers to increase universality and appeal. The E-E video was released on Stanford Medicine’s YouTube channel on March 21, 2020, and went viral within 24 h. After 10 days, it had reached 332,000 views on YouTube, 220,000 views on Instagram, 294,000 views on Facebook, and 402,000 views on Twitter, with a cumulative count of 1.2 million views [8]. The E-E video could play a useful role in disseminating evidence-based health recommendations related to COVID-19; however, its effectiveness remains unclear.

### Objectives

The study aims to achieve the following objectives. To establish:
The E-E video’s effectiveness in improving knowledge of preventive COVID-19 behaviorsThe E-E video’s effectiveness in increasing behavioral intent toward COVID-19 preventionPeople’s voluntary interest to watch the E-E video

### Trial design

The present study is a multi-site, parallel group, randomized controlled trial (RCT) comparing the effectiveness of the E-E video against an APC video or no video (Fig. 1) [9]. Randomization is at a 1:1:1 ratio for the three arms of the trial. Nested within each arm of the trial is a list experiment. Participants will be randomized at a 1:1 ratio to a control or treatment list. After completing the list experiment, participants in arms 2 and 3 will receive the E-E video to ensure post-trial access to treatment [10].

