#### Secondary outcome measure

We will assess participant’s behavioral intent to seek health information from online, animated videos. Because of social desirability bias, we will again use a list experiment with the same procedures described in Table 2. The list experiment will read: *This week, I will seek health information from: Television news channels; Social media celebrities; Religious leaders on the Internet; Public health agency websites; Conversations with family and friends; *Animated videos made by health experts*. (The sensitive item is indicated by an asterisk (*).)

We aim to measure participant engagement with the CoVideo. At the end of the survey, we will offer the APC and no-video arms the choice to watch the CoVideo or end the survey. The Gorilla platform will record this response. If the “Watch Video” button is clicked, Gorilla will record the time (in milliseconds) from the video start until the participant clicks the “Finish” button (or until the video ends at 2.30 min, whichever comes first). This data will be used to assess objective 3.

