#### Secondary outcomes

Using the same statistical procedure described above, we will assess behavioral intent to seek health information with E-E media. To establish participant engagement with the CoVideo, we will use a logistic regression model to estimate the proportion of participants in the APC and control arms that chose to watch the CoVideo, adjusting for the knowledge scores and demographic factors. We will use either an OLS model or Cox proportional hazards model to model the time to when a person clicks “Finish Video” (right censoring) or when the CoVideo ends naturally (left censoring). We will use R statistical software to undertake the analysis.

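### The trial design section has arms 2 and 3 receive the CoVideo, but objective 3 needs their recorded choice to watch it; the sections should be reconciled and that choice reported by arm

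*Protocol article*

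**What the plan says.** The protocol article describes what happens to arms 2 (APC video) and 3 (no video) after the outcome questions in three places.

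- **Trial design:** once the list experiment is done, "participants in arms 2 and 3 will receive the E-E video to ensure post-trial access to treatment". No option to decline is mentioned.
- **Secondary outcome measure:** "At the end of the survey, we will offer the APC and no-video arms the choice to watch the CoVideo or end the survey". It continues, "The Gorilla platform will record this response". For those who click to watch, "Gorilla will record the time (in milliseconds) from the video start until the participant clicks the" finish button, or until the video ends. The paragraph closes, "This data will be used to assess objective 3".
- **Statistical methods, Secondary outcomes:** a logistic regression is to "estimate the proportion of participants in the APC and control arms that chose to watch the CoVideo". The covariates named are the knowledge score and demographic factors. Viewing time gets a separate model.

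Objective 3 in the Objectives section is to establish people's "voluntary interest to watch the E-E video".

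The section explaining the comparators says that the APC video resembles the CoVideo: animated, wordless, with sound effects, and 2.30 min long.

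**The concern.** The design section reads as provision to everyone in arms 2 and 3. The outcome and analysis sections rely on some of those people declining. A reader of the article cannot tell from the text which procedure was programmed. Each reading makes another statement untrue: under provision to all there is no watch-or-decline outcome to analyse, and under a free choice those who end the survey have not received the video, contrary to the design section.

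There is a second issue in the same analysis. The two arms reach the offer with different experience. The no-video arm is deciding about its first animation in the survey, the APC arm about its second. The trial separates these arms elsewhere in order to isolate the effect of watching any video, but the analysis sentence for objective 3 names them together and gives no arm term.

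**Working it through.** **1. The two procedures side by side**

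| | Trial design | Secondary outcome measure and its analysis |
|---|---|---|
| Who | Arms 2 and 3 | Arms 2 and 3 |
| When | After the list experiment | At the end of the survey |
| What | The video is received | The video is offered; the person may end the survey instead |
| Purpose | Post-trial access | Data for objective 3 |

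The people are the same and the procedures differ. The article states no figure here that could be reproduced.

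**2. Consequence of a literal reading of the design section**

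Let Y = 1 if a participant chooses to watch. If all are shown the video, Y = 1 for everyone. The observed proportion is p = 1, its variance p(1 − p)/n is 0, and the logit ln[p/(1 − p)] has no finite value. The logistic model then has no maximum-likelihood estimate. Viewing time could still vary if people were able to click to finish early, so one of the two engagement measures might survive.

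**3. Consequence of the outcome section's procedure**

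Y varies and is logged, and viewing time is recorded for those who watch. Both measures for objective 3 are obtainable.

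**4. Primary outcomes**

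The design section places the CoVideo after the list experiment, and the outcome section places the offer at the end of the survey. Neither puts it before the list questions. The prose does not say whether the knowledge items come before the lists, and the schedule figure is not shown. Nothing in the text shows that a primary outcome is affected.

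**5. Naming the two arms together**

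Inputs: 17,010 participants (Sample size) and 1:1:1 allocation (Trial design).

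- Per arm: 17,010 / 3 = 5,670. Both arms: 2 × 5,670 = 11,340.
- Let p_a and p_c be the proportions choosing to watch in the APC and no-video arms. With equal arm sizes a combined proportion is (p_a + p_c)/2. It differs from p_c by (p_a − p_c)/2, and from p_a by the same amount in the other direction. The documents give no value for p_a − p_c.
- Worst-case standard error in one arm (p = 0.5): √(0.25 / 5,670) = 0.0066, or 0.66 percentage points.
- Worst-case standard error for both arms combined: √(0.25 / 11,340) = 0.0047, or 0.47 percentage points.

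Reporting by arm therefore loses about 0.2 percentage points of standard error per estimate at most, and the combined figure can still be given.

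**The case against.** The strongest defence is that the design sentence is only a loose summary. Its stated aim is to secure access, which an offer would satisfy, and the article lets participants leave at any time, so compulsory viewing is an unlikely reading. The detailed outcome and analysis sections agree with each other and with the objective. This stands, and it makes the matter a limited inconsistency. It does not remove the conflict, because the sentence as written says that both arms get the video.

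On the second issue, the defence is that the analysis sentence does not say the arms will be pooled, and that model details may sit in an analysis plan that is not shown. That is also fair: pooling is not established. But the sentence does list its covariates, and arm is not among them, so naming arm there is a useful clarification.

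Four stronger inferences are tempting and are not supported:

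- **That objective 3 cannot be measured.** This follows only from a literal reading of the design section, and then only for the proportion.
- **That the APC arm decides straight after its first video.** At least the list questions come between.
- **That combining the arms biases the result by a known amount.** Any figure would be an assumption about p_a − p_c.
- **That the no-video arm alone is the right answer to objective 3.** The objective concerns people's interest in general and does not restrict it to those who have seen no other video.

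**Conclusion.** The contradiction is real and concerns a secondary objective. Taken literally, the design section would leave no variation in the proportion choosing to watch, across all of arms 2 and 3 (about 11,340 people at full recruitment). Under the outcome and analysis sections objective 3 is measurable.

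Reporting by arm is a worthwhile improvement that costs almost nothing, because the APC arm has already watched a video of similar style. Whether this changes willingness to watch, and in which direction, cannot be derived from the documents. The precision figures assume the full 17,010 participants, equal allocation, and that everyone in the two arms reaches the offer. Early exits would reduce the numbers and raise the standard errors.

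**What to change.** 1. Reconcile the Trial design section with the Secondary outcome measure and Secondary outcomes sections, so that all describe the same procedure for arms 2 and 3, at the same point in the survey. The Trial status section reports 14,800 completed surveys, so the text should match what the platform actually presented.
2. In the Secondary outcomes analysis, include trial arm in the logistic model and report the proportion choosing to watch separately for the no-video and APC arms. A combined figure may be shown alongside.

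The cost is one sentence in the design section and one line in the analysis. No new data are needed, because arm is known from randomisation. The only loss is the slightly larger standard error of the single-arm estimates, at most about 0.66 instead of 0.47 percentage points.

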**Fig. 1 Fig1:**
[figure not shown]
The trial design, which consists of three arms. Participants will be randomly assigned (at a 1:1:1 ratio) to the E-E video (CoVideo, arm 1), an APC video (arm 2), or no video (arm 3). Each arm has a list experiment, with participants split (at a 1:1 ratio) into a control or treatment group

## Methods: participants, interventions, and outcomes

### Study setting

This will be an online study setting. We will use the online recruitment platform Prolific Academic (ProA: https://www.prolific.co) to enroll participants from the USA, the UK, Germany, Spain, Mexico, and France. We will host and deploy our study on an online platform called Gorilla™ (www.gorilla.sc) (Fig. 2).

**Fig. 2 Fig2:**
[figure not shown]
Schedule of enrolment, interventions, and assessments for the study

### Eligibility criteria

Registered participants on the ProA platform must be between the ages of 18 and 59 years (male, female, or other), have current residence in the target countries, and speak English, German, or Spanish.

### Ethical approval

Ethical approval was obtained from the Stanford University IRB on April 12, 2020, protocol #55820.

### Who will take informed consent?

Participants will undergo a process of informed consent on the ProA platform. The consent form explains the purpose of the study, the risks and benefits of the research, and how to contact the study investigators (or the Stanford University ethics review board) about problems experienced during the course of the study.

### Criteria for discontinuing or modifying allocated interventions

We will not discontinue or modify the allocated interventions during the course of the study. Participants may choose to discontinue their participation at any time.

## Interventions

### Intervention description

The intervention is an E-E video about COVID-19 prevention, which we abbreviate to CoVideo. Developed by our co-author (MA) for Stanford Medicine, the CoVideo is animated with sound effects and has no words, speech, or text. The CoVideo shows how the novel coronavirus is spread (airborne, physical contact) and recommends best practices to prevent onward transmission (staying at home, not congregating in public spaces, and sanitizing hands/surfaces). The CoVideo also covers the mass media coverage of the outbreak and the public’s response to this media coverage, which includes a subplot on the stockpiling of essential goods, and the impact thereof on healthcare services and resources (e.g., doctors being unable to access protective equipment). The CoVideo can be viewed at https://www.youtube.com/watch?v=rAj38E7vrS8.

### Explanation for the choice of comparators

The comparators are an APC video (arm 2) or no video (arm 3). The APC video is similar in style to the CoVideo; it is also animated with a duration of 2.30 min and has sound effects but no words, speech, or text. The video message is about how small choices become actions, which become habits, which become a way of life (https://www.youtube.com/watch?v=_HEnohs6yYw). The APC will enable us to quantify the attention effect of the CoVideo. APC conditions should mimic the “inactive” components of an intervention—the effect of watching the video—while not containing any of the “active” intervention components—the content delivered by the video [11]. To measure its total effect, we also compare the CoVideo with a control (no video). We do not assume the CoVideo is better than nothing; it is possible that the CoVideo could motivate reactance to our message about COVID-19 prevention [12–14]. For the list experiments, we will use the control list as the comparator.

### Outcomes

#### Primary outcome measures

There are two primary outcome measures. First, we will use 18 True/False questions to assess if the CoVideo improves knowledge about preventive COVID-19 behaviors. These questions are shown in Table 1 and this data will be used to assess objective 1.

**Table 1 Tab1:** The COVID-19 knowledge items, which require True/False responses

The current coronavirus can be spread by an infected person even if they look healthy	Cleaning surfaces with soap and water is an effective way to kill the current coronavirus
The current coronavirus cannot be spread from person to person	An effective way to prevent COVID-19 spread is to wear a face mask even if you do not have COVID-19 symptoms
The current coronavirus cannot survive on surfaces for more than a few minutes	An effective way to prevent COVID-19 spread is to wash your hands frequently with soap and water
Some people with COVID-19 infection may experience a cough	An effective way to prevent COVID-19 spread is to regularly rinse your nose with salt water
Some people with COVID-19 infection do not experience a fever	An effective way to prevent COVID-19 spread is to avoid touching your face
The current coronavirus spreads from person to person through small droplets from the mouth	An effective way to prevent COVID-19 spread is to avoid shaking hands with other people
The current coronavirus spreads from person to person through small droplets from the nose	An effective way to prevent COVID-19 spread is to avoid places that are crowded with people (like bars, restaurants, or performances)
You can catch COVID-19 by touching a contaminated surface and then touching your face	An effective way to prevent COVID-19 spread is to eat garlic with each meal
Antibiotics can be used to treat COVID-19 infection	An effective way to prevent COVID-19 spread is to avoid sharing eating utensils with others

Second, we will assess if the CoVideo improves behavioral intent toward preventive COVID-19 behaviors. Since many participants will be primed to give socially desirable answers to the behavioral intent questions, we will use a list randomization approach [15–17]. There will be five list experiments, which are shown in Table 2. For each experiment, the control group will receive a list of five items. Participants will be asked to state *how many* of the items they agree with, without stating which ones they agree with. For the first list experiment, imagine that the control group selects an average of 2 out of the 5 items. The treatment group will get the same list but with one additional “sensitive” item about behavioral intent. Using the example, the participants in the treatment group select an average of 2.2 out of the 6 items. Holding all else equal, we conclude that the prevalence of participants that would go out with friends (item 6 of list 1 in Table 2), in defiance of lockdown regulations, is 20%. We designed the list experiments in line with best practices [17], and we will use this data to assess objective 2.

**Table 2 Tab2:** In each trial arm, both groups will receive five lists. For each list, the control group will get the first five items only; the treatment group will receive the five items and the sixth sensitive item, indicated by an asterisk (*). Each list experiment will be preceded by the question: “How many of the five/six statements do you agree with? We don’t want to know which ones, just answer how many. This week I will spend time watching TV, etc.”

**List 1: Social distancing**	**List 2: Wash hands**
1. Spend time watching TV	1. Clip my toenails
2. Do the vacuuming	2. Spend time watching movies
3. Pick a fight with my partner	3. Clean the toilet
4. Eat a low sugar diet	4. Smoke marijuana
5. Rinse my nose with salt water daily	5. Eat fruit daily
*6. Go out with my friends**	*6. Wash my hands frequently**
**List 3: Clean surfaces**	**List 4: Share utensils**
1. Watch a new TV series	1. Spend time on the Internet
2. Spend time gardening by myself	2. Do daily indoor exercises
3. Try to go vegetarian	3. Take an online course
4. Have alcoholic drinks on at least three evenings	4. Play a prank on my partner
5. Catch up on last week’s work	5. Smoke cigarettes
*6. Clean kitchen counters after use**	*6. Clean my dishes after use**
**List 5: Stockpiling**	
1. Spend time chatting with my friends online	
2. Try new cooking recipes	
3. Watch a pornographic movie	
4. Clean all floor surfaces	
5. Visit the World Health Organization (WHO) website	
*6. Stock up on household supplies for a month**	

#### Secondary outcome measure

We will assess participant’s behavioral intent to seek health information from online, animated videos. Because of social desirability bias, we will again use a list experiment with the same procedures described in Table 2. The list experiment will read: *This week, I will seek health information from: Television news channels; Social media celebrities; Religious leaders on the Internet; Public health agency websites; Conversations with family and friends; *Animated videos made by health experts*. (The sensitive item is indicated by an asterisk (*).)

We aim to measure participant engagement with the CoVideo. At the end of the survey, we will offer the APC and no-video arms the choice to watch the CoVideo or end the survey. The Gorilla platform will record this response. If the “Watch Video” button is clicked, Gorilla will record the time (in milliseconds) from the video start until the participant clicks the “Finish” button (or until the video ends at 2.30 min, whichever comes first). This data will be used to assess objective 3.

### Sample size

We calculated the sample size needed for pairwise comparisons between three groups using a one-way analysis of variance (ANOVA). The formula to calculate the sample size is [18]:

$$ {n}_A=\left({\sigma}_A^2+{\sigma}_B^2/\kappa \right){\left(\frac{Z_{1-\frac{\alpha }{\tau }}+{Z}_{1-\beta }}{\mu_A-{\mu}_B}\right)}^2 $$where *κ* = 1, which is the matching ratio; *μ*_*A*_ and *μ*_*B*_ are the group A and B means; *σ*_*A*_ and *σ*_*B*_ are the group A and B standard deviations; *α* = 0.05 is the type-I error; *β* = 0.20 is the type-II error; *Z* is the quantile function; and *τ* = 2 is the number of comparisons to be made. To detect a small difference of 0.1 between the knowledge scores of two trial arms, we assumed a mean of *μ*_*A*_ = 14.0 and *μ*_*B*_ = 14.1 and *σ*_*A*_ = 1.5 and *σ*_*B*_ = 1.5. We select *μ* on the expectation that participants will get 14 out of 18 knowledge items correct. This gives a sample size of *n*_*A*_ = *n*_*B*_ = *n*_*C*_ = 3,532, so *N* = 10,596. If we change our assumption about *σ* and increase it to *σ* = 1.8, then the required sample size becomes *n*_*A*_ = *n*_*B*_ = *n*_*C*_ = 5,087 and *N* = 15,261. For the list experiment, we selected a sample size to detect a small difference of 0.05 between the control list group and the treatment list group. Because we framed the list questions to avoid floor and ceiling effects, we expect, on average, that the control group will agree with 2 out of the 5 items and the treatment group 2.05 of the 6 items. We selected *σ*_*A*_ = 0.7 and *σ*_*B*_ = 0.8, allowing the second *σ* to be larger because of the additional sensitive item. This calculation gives a sample size of *n*_*A*_ = *n*_*B*_ = *n*_*C*_ = 3,548 and *N*= 10,644. If we change our assumption about *σ* and increase it to *σ*_*A*_ = 0.9 and *σ*_*B*_ = 1.0, then we have *n*_*A*_ = *n*_*B*_ = *n*_*C*_ = 4,553 and *N* = 13,659. For this study, we will recruit 17,010 participants, more than the 15,261 calculated sample size, to ensure our study is sufficiently powered.

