#### Primary outcomes

For each participant, we will sum the knowledge items that are correctly answered (min. = 0, max. = 18). We will then obtain the mean knowledge score for each trial arm. Let $$ {\overline{K}}_k $$ denote the mean knowledge score for the *k*th trial arm, where *k* ∈ {*v*, *a*, *c*} such that *v* represents the CoVideo, *a* represents the APC, and *c* represents the control. We will use an ordinary least squares (OLS) regression model to estimate $$ {\overline{K}}_k $$ as well as obtain the difference estimators. We define the difference between the CoVideo ($$ {\overline{K}}_v\Big) $$ and the control ($$ {\overline{K}}_c\Big) $$ as the total effect, the difference between the CoVideo ($$ {\overline{K}}_v\Big) $$ and the APC ($$ {\overline{K}}_a\Big) $$ as the content effect, and the difference between the APC video ($$ {\overline{K}}_a\Big) $$ and the control ($$ {\overline{K}}_c\Big) $$ as the attention effect.

For each list experiment, we will calculate the mean score for the control list, denoted by $$ \overline{C_i} $$, and the mean score for the treatment list, denoted by $$ \overline{T_i} $$, for the *i*th list experiment (*i* = 1, …, 5). We will then estimate the difference between the treatment and control list for each trial arm, denoted by $$ {D}_{ik}={\overline{T}}_{ik}-{\overline{C}}_{ik} $$, for the *i*th treatment list and *k*th trial arm, where *k* ∈ {*v*, *a*, *c*}. Let $$ D{D}_i^T $$ denote the total effect, which is estimated by *D*_*iv*_ − *D*_*ic*_; let $$ D{D}_i^C $$ denote the content effect, which is estimated by *D*_*iv*_ − *D*_*ia*_; and let $$ D{D}_i^A $$ denote the attention effect, which is estimated by *D*_*ia*_ − *D*_*ic*_. These analyses are analogous to difference-in-difference analyses, which can be implemented by specifying the appropriate main and interaction terms in an OLS regression.

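### The division by τ = 2 in the sample-size formula only yields the ordinary two-sided 5% critical value, so the quoted sizes make no allowance for multiple comparisons, and three contrasts are planned

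*Protocol article*

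**What the plan says.** The Sample size section describes the calculation as one for "pairwise comparisons between three groups using a one-way analysis of variance (ANOVA"). Its inputs are "α* = 0.05 is the type-I error" and "β* = 0.20 is the type-II error". The critical value is the normal quantile at 1 − α/τ, with the explanation that "τ* = 2 is the number of comparisons to be made".

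For a knowledge difference of 0.1 it reports 3,532 per arm (N = 10,596) at SD 1.5 and 5,087 per arm (N = 15,261) at SD 1.8. The recruitment target of 17,010 is justified as exceeding 15,261.

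The Primary outcomes part of Statistical methods defines three differences between arms: CoVideo minus control, CoVideo minus APC, and APC minus control. The second and third appear in the words "as the content effect, and the difference between the APC video". The same three contrasts are defined for each of the five lists.

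Sidedness is not stated. The comparator section says "We do not assume the CoVideo is better than nothing; it is possible that the CoVideo could motivate reactance".

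**The concern.** A reader takes τ to be a Bonferroni divisor that makes the sizes valid for several comparisons. Two things conflict with that.

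- **The critical value.** A two-sided test already halves α. Dividing by 2 once and calling it the number of comparisons leaves either the tails or the multiplicity unpaid.
- **The count.** Three arms give three pairs, and the analysis section defines all three as effects on the primary outcomes. It does not rank them or mark any as descriptive.

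The protocol's assurance that 17,010 is enough is at stake. It rests on 15,261, which is correct only if each contrast is tested at an unadjusted 5%. If the contrasts are to share a 5% error rate through the split that the formula appears to make, the trial has less than 80% power in the scenario used to set its size. A null content or attention effect would then be weaker evidence than the protocol implies.

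**Working it through.** **Inputs (Sample size section unless noted).** α = 0.05; power 0.80; τ = 2; knowledge difference 0.1; SD 1.5 or 1.8 in each arm; equal allocation; 17,010 / 3 = 5,670 per arm. Three contrasts (Primary outcomes).

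**Formula.** With equal SDs and tail area *a*:

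n per arm = 2σ² (z(1−a) + 0.8416)² / 0.1²

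**Step 1: reproduce the printed figures.** With a = α/τ = 0.05/2 = 0.025, z = 1.960 and (1.960 + 0.8416)² = 7.849.

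- SD 1.5: 2 × 2.25 × 7.849 / 0.01 = 3,532, as printed.
- SD 1.8: 2 × 3.24 × 7.849 / 0.01 = 5,086.1, rounded up to 5,087, as printed.

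These are the sizes for one two-sided 5% comparison of two arms.

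**Step 2: try the other tail areas.**

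| Reading | Tail area | z | n per arm, SD 1.5 | N | n per arm, SD 1.8 | N |
|---|---|---|---|---|---|---|
| Two-sided, one comparison | 0.025 | 1.960 | 3,532 | 10,596 | 5,087 | 15,261 |
| Two-sided, τ = 2 | 0.05/4 = 0.0125 | 2.241 | 4,278 | 12,834 | 6,160 | 18,480 |
| Two-sided, τ = 3 | 0.05/6 = 0.00833 | 2.394 | 4,712 | 14,136 | 6,784 | 20,352 |
| One-sided, one comparison | 0.05 | 1.645 | 2,783 | 8,349 | 4,007 | 12,021 |
| One-sided, τ = 3 | 0.05/3 = 0.01667 | 2.128 | 3,969 | 11,907 | 5,715 | 17,145 |

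Only tail area 0.025 gives the printed sizes. A one-sided test split over two comparisons also has tail area 0.025, so arithmetic alone cannot separate that reading from the unadjusted two-sided one. The next field deals with it.

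**Step 3: power at the planned 5,670 per arm.** Power = Φ(0.1 / (σ√(2/5,670)) − z).

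- SD 1.8: the standardised difference is 2.958. Unadjusted: Φ(2.958 − 1.960) = 84.1%. Two-sided τ = 2: Φ(2.958 − 2.241) = 76.3%. Two-sided τ = 3: Φ(2.958 − 2.394) = 71.4%.
- SD 1.5: the standardised difference is 3.550. The corresponding powers are 94.4%, 90.5% and 87.6%.

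**Step 4: power at the protocol's own sizes.** At 3,532 (SD 1.5) or 5,087 (SD 1.8) per arm, two-sided power is 80% unadjusted, about 71% with τ = 2 and about 66% with τ = 3.

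**Step 5: list experiments.** The same formula gives the printed 3,548 for a difference of 0.05 with SDs 0.7 and 0.8, again at tail area 0.025: (0.49 + 0.64) × 7.849 / 0.0025 = 3,547.7. With two-sided adjustment this becomes 4,297 (τ = 2) or 4,733 (τ = 3). The list sizes therefore share the defect.

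**The case against.** **One-sided reading.** Sidedness is never stated, and the objectives are worded as improvement. If tests are one-sided, α/2 is exactly a Bonferroni split for two comparisons, as the text says. This is the best defence, but it does not hold. The comparator section says "We do not assume the CoVideo is better than nothing" and allows for a reaction against the message, so harm must be detectable. The attention effect has no stated direction. Even if one-sided testing is granted, three contrasts need N = 17,145 at SD 1.8, just above 17,010 (power 79.7%).

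**Two comparisons, not three.** The trial is introduced as the CoVideo against APC and against no video. The attention effect does not involve the CoVideo, answers no listed objective, and equals the total effect minus the content effect. It could reasonably be descriptive, and τ = 2 would then be a fair count. The protocol does not say so. With τ = 2 and two-sided tests, the SD 1.8 case still needs 18,480.

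**An α split is not the only route.** With exactly three groups, unadjusted pairwise tests after a significant overall 5% test control the familywise error, and the section mentions ANOVA. A simulation at 5,670 per arm and SD 1.8 gives about 81% power for a 0.1 difference when the third arm equals one of the other two, and about 75% when it lies midway. A fixed sequence would also avoid a split. Both options are legitimate and could be chosen in an SAP, but the protocol states neither, and its analysis is an OLS model with no overall gate. Under either option τ would still be mislabelled.

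**Small practical effect.** This stands in part. At SD 1.5 every adjusted N is below 17,010. The shortfall is confined to SD 1.8, but that is the case on which the protocol rests its recruitment figure.

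**Conclusion.** The concern holds. The knowledge sizes are right for one unadjusted two-sided 5% comparison and wrong for what the section says they cover. The claim that 17,010 exceeds the requirement fails at SD 1.8 once the adjustment is made: the shortfall is 18,480 − 17,010 = 1,470 participants for two contrasts, or 20,352 − 17,010 = 3,342 for three.

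This rests on two-sided testing, which is inferred from the comparator section, and on a Bonferroni split, which is what a divisor described as the number of comparisons implies. The τ = 3 figures apply if all three contrasts are confirmatory, and the τ = 2 figures if the attention effect is descriptive. The trial is not undermined: at SD 1.5 it keeps 88% to 90% power for the knowledge outcome under either count.

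**What to change.** State that tests are two-sided and which contrasts are confirmatory. Then take one of two routes.

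1. **Split α.** Write the critical value as the normal quantile at 1 − α/(2τ), with τ = 3, or τ = 2 if the attention effect is declared descriptive. Restate n and N from the table above, and report power at 5,670 per arm for both SDs.
2. **Use a fixed-sequence test.** Give the order of the contrasts, remove τ, and say the sizes are for a single two-sided 5% comparison.

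Apply the same route to the list-experiment sizes, which use the same formula. When restating them, also recheck the printed 4,553: SDs of 0.9 and 1.0 give 5,683 in the formula as it stands, whereas 0.9 and 0.8 give 4,553.

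Keep the recruitment target at 17,010; the Trial status section already reports 14,800 completed surveys. The change is to the text only and adds no participants. Under the first route, the cost is that stated power for knowledge at SD 1.8 becomes 71% to 76%. The choice should be fixed before the data are analysed.
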